### Manufacturing of BMMNCs/placebo

Following informed consent all patients undergo a bone marrow extraction through repeated aspirations from the posterior iliac crest to a total volume of 100–180 mL using 5 mL syringes (20–30 aspirations) that will be collected in an sterile plastic bag containing ACD-A (1:5 v/v proportion). The entire extraction procedure lapses 20–30 min. BMMNCs are obtained by density gradient centrifugation over Ficoll-Hypaque in an automated cell processor SEPAX (Biosafe). After two washes with a 4% albumin solution, a 50 ml cell suspension will be filtered (50 μm diameter), and aliquots used for cell count, viability tests, microbiological assays and biological determinations (immune phenotype and chemotactic ability tests). From this point onwards, the procedure proceeds as follows: For the experimental group, the cell suspension undergoes a final centrifugation, is re-suspended in 20 ml of lactate Ringer’s solution (containing 1% human albumin and 2.5% glucose) and filtered by a 50 μm filter. The total dose of BMMNCs is within the range of 5-10 × 10^8^ cells. Cell expansion is not used in this protocol. In our previous pilot experience, the minimum percentage of BMMNC recovery after processing was around 20–30% of the total initial cell count, which is enough to obtain a final cellular number in the order of 5–10 × 10^8^ to be infused. Should the number of cells harvested in the final product be insufficient, patient’s data would be excluded from the efficacy analysis. Cell viability is > 95% of BMMNCs, and this concentration is maintained for 24 h at a temperature between 4 °C and 22 °C degrees centigrade, as it has been validated in our laboratory. For the control group, placebo consists of 20 ml of lactate Ringer’s solution (containing 1% human albumin and 2.5% glucose), plus the required volume of red blood cells from the extracted bone marrow, to adjust the hematocrit to 1% for masking purposes. The pre-processed BMMNCs from patients in the control group is re-suspended in a solution containing 4% albumin and 10% dimethylsulfoxide and cryopreserved for future administration via compassionated use (if efficacy data is conclusive after trial interim/final analysis). The autologous BMMNCs or placebo is placed in 2–3 sterile syringes (depending on coronary artery dominance) and is transported to the cardiac units in the participating sites for the infusion procedure.

### BMMNCs infusion

The administration of placebo or cell product is performed within 6–8 h after product processing. A 10 mL volume is delivered in a single dose through the three main coronary arteries: anterior descending, circumflex and right coronary artery. Fifty percent of the dose is administered through the anterior descending artery and the other 50% through the right or circumflex coronary artery, depending on the dominance. If a clear dominance is absent, 25% is administered through the right artery, and 25% through the circumflex artery. Exceptionally, in case of hypoplasia of the descending artery, the product is administered in the same proportions (33%) though the three coronary arteries.

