### BMMNCs biological characterization

To analyze biological predictive factors of response to treatment [27], aliquots of the cellular suspension infused to experimental group patient are obtained for the following purposes:
Automatic cell count for evaluation of total infused cellularity.Immune phenotype characterization: BMMNCs aliquots (1–5 × 10^5^ cells) are stained with fluorochrome-conjugated monoclonal antibodies (FITC, PE and APC) against human cell surface markers CD34, CD133, VEGFR2, CXCR4, CD90, CD38, CD117, HLA-DR, CD45, CD105, CD73, CD14. After incubation for 15 min in darkness, BMMNCs are washed with PBS and centrifuged for 5 min at 1800 rpm. The cell pellet is then resuspended in PBS, stained with Propidium Iodide (Miltenyi Biotec) to measure cellular viability as analyzed with MACSQuant cytometer (using MACSQuantify software for quantitative measurements).Cell chemotactic ability: BMMNCs migration in response to VEGF (R&D Systems, Inc., Minneapolis) and SDF-1 (R&D Systems, Inc., Minneapolis) was assessed using 24-well culture plates and 8 μm pore size inserts (BD Biosciences, Erembodegem, Belgium). A dose of 5 × 10^4^ cells is placed in the system using serum free media RPMI-1640 (BioWhittaker® LONZA, Verviers, Belgium) and 100 ng/ml of VEGF, 100 ng/ml SDF-1 or nothing (control well). After 24 h of incubation at 37 °C, cell migration is quantified using a Neubauer chamber.

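### The product is made up in 20 mL but the infusion section delivers 10 mL, and nothing in the article reconciles the two with the stated cell dose

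*Protocol article*

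**What the plan says.** Protocol article, section Manufacturing of BMMNCs/placebo: in the experimental arm "the cell suspension undergoes a final centrifugation, is re-suspended in 20 ml of lactate" Ringer's solution, and for controls "placebo consists of 20 ml of lactate Ringer’s solution (containing 1% human albumin and 2.5% glucose", plus red cells for masking. The same section states: "The total dose of BMMNCs is within the range of 5-10 × 10^8^ cells". It makes clear that this is the number meant to reach the patient, since it calls the expected recovery one "which is enough to obtain a final cellular number in the order of 5–10 × 10^8^ to be infused". The finished product goes into two or three syringes, depending on coronary dominance. No volume per syringe is given.

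Section BMMNCs infusion: "A 10 mL volume is delivered in a single dose through the three main coronary arteries". It then divides the dose: "Fifty percent of the dose is administered through the anterior descending artery and the other 50% through the right or circumflex coronary artery", depending on dominance. Without clear dominance the split is 50/25/25 over three arteries, and with a hypoplastic descending artery it is 33% each.

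Three other places depend on the dose:
- The Discussion describes the trial as one of high-dose cells and repeats the 5–10 × 10^8 range.
- BMMNCs biological characterization lists, as a possible predictor of response, "Automatic cell count for evaluation of total infused cellularity".
- The manufacturing section removes patients from the efficacy analysis when the final product holds too few cells.

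**The concern.** The cell dose defines the experimental intervention. Adjacent sections give two explicit volumes that cannot both describe the whole dose: 20 mL prepared and 10 mL delivered. The stated dose is tied to the prepared product. If only half of that product is given, the dose received is half of what the article reports.

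Three things depend on which volume applies:
- **Description of the intervention.** A factor of two decides whether the stated high-dose range is what patients received.
- **Infused cellularity.** A count for the whole product equals the infused number only if the whole product is infused.
- **Exclusion for insufficient cells.** The rule refers to the final product. A product can meet the stated range while the volume delivered from it does not.

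**Working it through.** **Inputs.** Final volume 20 mL and total dose 5–10 × 10^8 cells (Manufacturing of BMMNCs/placebo); delivered volume 10 mL and splits 50/50, 50/25/25 and 33% each (BMMNCs infusion). Assumptions: a uniform suspension, and no concentration step after the 20 mL re-suspension (none is described).

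**Step 1, the plan's own figure.** Concentration = total cells / prepared volume:
- 5 × 10^8 / 20 mL = 2.5 × 10^7 per mL
- 10 × 10^8 / 20 mL = 5 × 10^7 per mL

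Delivering all 20 mL returns 5–10 × 10^8 cells, as stated.

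**Step 2, the 10 mL sentence taken literally.** Cells delivered = concentration × 10 mL:
- 2.5 × 10^7 × 10 = 2.5 × 10^8
- 5 × 10^7 × 10 = 5 × 10^8

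The result is 2.5–5 × 10^8, a share of 10/20 = 50%. Only the maximum yield reaches the stated minimum of 5 × 10^8, and it equals that minimum exactly.

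**Step 3, the converse.** If 10 mL carried the full 5–10 × 10^8, then 20 mL at that concentration would hold (5–10 × 10^8) / 10 × 20 = 10–20 × 10^8 cells. The article gives no such total.

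**Step 4, can sampling explain the missing 10 mL?** The aliquots listed under manufacturing come from the 50 mL suspension, before the 20 mL step. The section on biological characterization takes aliquots from the infused suspension, but with 1–5 × 10^5 cells per staining and 5 × 10^4 in the migration assay. Half of the smallest product is 2.5 × 10^8 cells, so it would take 2.5 × 10^8 / 5 × 10^5 = 500 of the largest staining aliquots to use it up. Sampling does not close the gap.

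**Step 5, does 10 mL per artery or per syringe work?**

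| Split | Volumes if 20 mL is given | Volumes if 10 mL is given | Fixed 10 mL per artery or syringe |
|---|---|---|---|
| 50/50 | 10 + 10 | 5 + 5 | 2 × 10 = 20 mL: fits |
| 50/25/25 | 10 + 5 + 5 | 5 + 2.5 + 2.5 | 3 × 10 = 30 mL: exceeds the product, and the portions are not equal |
| 33% each | 6.7 × 3 | 3.3 × 3 | 3 × 10 = 30 mL: exceeds the product |

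The per-artery reading fits the two-artery case only. The sentence itself attaches 10 mL to the single dose through all three arteries.

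**The case against.** The strongest reply is that the dose is specified in cells, and consistently so: twice under manufacturing and again in the Discussion. The infusion section distributes the whole dose, and nothing describes keeping or discarding half of it. Half of 20 mL is 10 mL, which fits two syringes and the 50/50 split, so the 10 mL may be a misplaced per-artery figure. That is plausible, and it is why the article cannot be read as evidence of under-dosing. It does not remove the conflict, because the sentence does not say per artery and the three-artery splits do not fit it.

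A reader might infer more than the text supports:
- **Two arteries against three.** This is not a contradiction. The number of arteries follows dominance and anatomy, and two or three syringes agree with that.
- **Different doses at different sites.** Syringes are filled before transport, and no text has sites measure out 10 mL. Table 2 also shows 24 of 28 enrolled patients at one hospital.
- **An invalid dose-response analysis.** No such analysis is described beyond cellularity as one of several response predictors. A constant factor of one half would mis-scale the variable but leave correlations and ranks unchanged.
- **A biased primary comparison.** Both arms are made up in 20 mL, so the mismatch alone does not disturb volume matching or blinding.
- **A missing record of delivered volume.** The case report form and full protocol are not shown, so no gap there can be claimed.

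**Conclusion.** The inconsistency stands: 20 mL prepared, 10 mL delivered, one stated cell dose, and no statement that links them. Its size is a factor of two, 2.5–5 × 10^8 against 5–10 × 10^8 cells, if the 10 mL sentence is literal, the suspension uniform and no further concentration takes place. If all 20 mL is given, the stated dose is met and the error lies in the volume sentence. The document does not settle which holds.

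The consequence for the exclusion rule depends on its threshold, which the article does not give. If the threshold were the lower limit of 5 × 10^8 and applied to delivered cells, a product given as 10 of 20 mL would need 10 × 10^8 cells to pass. Applied to the product, it would need 5 × 10^8.

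This is more than clerical, because the figure defines the intervention. It is not a finding about what patients actually received.

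**What to change.** Reconcile the manufacturing and infusion sections so that four items agree: the prepared volume, the delivered volume (stated as total, per artery or per syringe), the way it is divided under each of the three splits, and the cell dose. State whether the 5–10 × 10^8 range and the exclusion for insufficient cells refer to the prepared product or to what is infused. Which volume or dose is right is for the sponsor and clinical team to state.

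Check the infusion records of the 27 patients already treated (Trial status) for the volume delivered. Base infused cellularity on concentration in the final product × volume actually delivered.

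The cost is small: a text correction and a review of 27 records. If the full protocol is already clear, only the article needs correcting. If it carries the same conflict, the change needs authorisation from the ethics committee and the medicines agency, as the Ethics and dissemination section requires for any modification.

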### Angiographic measurement of ventricular function

Angiographic changes in global LVEF at 6 months after cell infusion is the primary endpoint of the trial. Cardiac catheterization is performed to measure systemic and left ventricular end-diastolic pressure, left ventricular function, and coronary flow reserve for each coronary artery as previously published [32]. The left ventricular function studies are based on the analysis of at least one left ventricular angiogram at a 30° right anterior oblique projection. For each ventriculogram measurements, a sinus beat and a post-extrasystolic beat are obtained for the establishment of the contractile reserve of the ventricle. An expert angiographer, blind to treatment allocation and patient progression, will draw the end-diastolic and end-systolic silhouettes using the CASS system. The left ventricular volumes and LVEF are determined and the regional wall motility is analysed. Sheehan’s method [38] is used to study asynergy, dividing the superimposed silhouettes by 100 radii of systolic wall shortening, from end-diastole to end-systole. The abnormal contracting segment is defined as the percentage of radii showing akinesia or dyskinesia. The mitral valve function is evaluated and, when present, mitral insufficiency is graded according to severity.

### Echocardiographic measurement of ventricular function

Echocardiography is used as a secondary endpoint for the purpose of comparison with published trials, as well as to provide additional non-invasive time points of LVEF evaluation. LV function will be measured with echocardiography at baseline (visit 1) as well as 6 (visit 5), 12 (visit 6), 18 (visit 7) and 24 (visit 8) months after infusion, using standardized imaging protocols to calculate ejection fraction using the Simpson’s rule. Although a discrete positive correlation has been described among LV angiography and echocardiography estimates [39], LVEF measurements by various techniques are generally not interchangeable [40]. However, LVEF changes trends measured with LV angiography will be compared with those obtained using echocardiography, and the intra-subject correlation among both LVEF estimates will be analyzed in order to stablish a correlation that may help explain the long and short-term effects of BMMNC.

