## Methods and design

### Trial design

The study is designed as randomized, placebo-controlled, double-blind phase IIb clinical trial to compare the functional recovery of patients receiving the conventional treatment for DC in combination with an intracoronary infusion of BMMNCs, using placebo as a control. A 2:1 BMMNC/placebo allocation ratio is used for the randomization of a total of 51 eligible patients. Therefore, a total of 34 subjects will receive BMMNCs infusion, whereas 17 subjects will be treated with a placebo infusion. In order to analyse the predictors of clinical response as well as safety variables, all trial subjects (*n* = 51) are followed for a period of 24 months, completing a total of nine study visits: screening (visit 1), randomization (visit 2), infusion (visit 3), 24 post-infusion (visit 3.1), and months 3 (visit 4), 6 (visit 5), 12 (visit 6), 18 (visit 7) and 24 (visit 8) after the BMMNC/placebo administration (Fig. 1). To allow for sample size re-calculation an interim analysis will be performed with the data from the 6 months post-infusion period of the first 20 patients included. A second interim analysis is planned when the last patient included in the trial has completed study visit 5 (6 months). This early analysis of the data may provide conclusive efficacy (and safety) evidence in order to allow for the authorization of compassionate treatment of finalized patients allocated to placebo. On-completion of protocol standardized 24 months’ follow-up, all patients receiving the experimental treatment will be followed on an observational scheme for an additional period of up to 5 years. This extended follow-up period will provide long term efficacy and safety data of BMMNCs infusion.

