### Study outcomes

The main study variable is the improvement on the ventricular function measured angiographicaly as described below. This efficacy outcome is measured as the changes on the LVEF evaluated by a cardiologist blinded to the patients’ clinical follow-up. With this objective, patients undergo cardiac catheterization in two study timepoints: on the date of the intracoronary infusion of either experimental treatment or placebo (visit 3) and at month 6 (visit 5) after infusion.

Secondary efficacy outcomes include clinical evaluation and NYHA functional grade, BNP or N-terminal fragment of pro-brain natriuretic peptide (NT-proBNP) blood levels, echocardiogram, exercise testing according to Naughton protocol, without oxygen consumption as well as biological parameters of the BMMNC product that may predict a good response (cellularity, chemotaxis and stem cell markers: CD133+, CD34+, CD34+/CD177+,CD34+/CD38-, CD34+/CXCR4+, CD34+/DR-, VEGFR2+, CD90+, CD105+, CD73+, CD14-, CD45-).

Study variables regarding safety are measured as appropriate during follow-up visits: adverse events (AEs) and serious adverse events (SAEs), causally related with study interventions or procedures (including marked changes of vital signs, abnormalities physical examinations and out of range laboratory test results). Additionally, the protocol emphasizes the identification of specific adverse events: major cardiac events or MACEs (defined as cardiac death, major arrhythmia, inclusion in heart transplant waiting list, cardiac resynchronization therapy interventions and hospital admission due to clinically relevant adverse cardiac events), symptoms and signs of arrhythmia, evidence of myocardial harm and tumoral biomarkers abnormalities.

The study design, evaluations and assessment timeline for all variables is illustrated in Fig. 1. After product infusion, all patients are followed-up for 24 months according to protocol by interventional or clinical cardiologists at the participating hospitals. Protocol programmed visits are structured in 9 time-points that include two pre-infusion visits (screening and randomization), BMMNC/placebo infusion day, and 6 post-infusion follow-up evaluation time-points according to a decreasing frequency: 24 h, 3 months, 6 months, 12 months, 18 months and 24 months. Trial investigators must ensure that essential clinical, analytical and exploratory data is registered in the study’s Case Report Form (CRF).

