### Study population and enrolment

The study population is constituted by adult male and female patients diagnosed with idiopathic DC, meeting all eligibility criteria as described in Table 1. A sample size of 51 subjects who are regularly followed-up in the Cardiology Units of the eight participating University Hospitals from the Andalusian Public Health System (Table 2) are included in the study through a competitive recruitment scheme. Before undergoing any trial-related procedures, all patients willing to participate in the study must sign a written informed consent. Study practitioners provide them with information about the study, the investigational product, the purpose, procedures and potential risks and benefits of the study. They are randomly assigned to the experimental or control group following a 2:1 ratio, and are engaged to complete study follow-up visits through an optimised medical attention. Trial subjects can withdraw consent for trial participation at any time. Once the patient has received treatment, withdrawal of consent is the single exclusion criteria considered by the protocol. In all other cases the patient must complete follow-up visits to meet at least safety objectives. In addition, patients who have not received the investigational product infusion can also leave the study when a SAE occurs, or the clinical situation of the patient changes and the investigator considers that an alternative treatment is needed.

**Table 1 Tab1:** Eligibility criteria

INCLUSION CRITERIA	
*Participants meeting all the following criteria will be included:*	
1. Male and female patients between 18 and 70 years old.	
2. Patients who sign the informed consent.	
3. Patient diagnosed with idiopathic dilated cardiomyopathy (using echocardiography).	
4. At least 6 months since dilated cardiomyopathy diagnosis.	
5. Lack of coronary injuries on multi-slice computerized axial tomography scan and/or hemodynamic study performed after the inclusion of the patient in the trial, or prior to recruitment if the patient does not present any angina symptomatology.	
6. Patients under optimised pharmacological treatment for at least 6 months prior inclusion in the trial.	
7. Left ventricular ejection fraction (LVEF) ≤ 40% or LVEF 40–50% if left ventricular end diastolic volume (LVEDV) > 110 ml/m^2^ (measured by echocardiogram).	
8. Presence of sinus rhythm.	

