### Data management and statistical analysis

Clinical data is manually registered using a paper Case Report Form (CRF). CRF data is entered in the study database using an Electronic Data Capture (EDC) system. After double data entry, resolution of all inconsistencies, and coding by means of medical dictionaries, a final quality control process will be applied. In case of compliance, the database will be considered error free and will be frozen for the statistical analysis of the data. Sponsor and investigator will have access to the final trial dataset.

A descriptive analysis will be performed including all demographic variables collected, as well as baseline clinical data. Qualitative variables will be summarized using absolute frequencies and percentages, while quantitative variables will be described using the mean, median, standard deviation, maximum, minimum and number of observations.

The efficacy evaluation of quantitative parameters will be performed by comparing basal values (prior to the administration of the product) with those recorded in the follow-up visits, using the paired Student’s t-test (if the variable meets the normality requirements), or the Wilcoxon paired test for all other cases. For qualitative parameters, the Chi-square test will be used.

Two interim analyses will be performed during the study. The first one, to ensure the statistical power of the study, will be performed when the first 20 patients reach a minimum follow-up of 6 months, and will include a new sample size calculation based on these data. In the second one, the main variable under study will be analysed once 6-months of follow-up have been completed in all patients recruited. If the results are positive, patients randomised to the control group will be treated via compassionate-use basis with their own cryopreserved BMMNCs, as early mentioned. Per-protocol analysis (PPA) will be used for all efficacy assessments. All p-values and confidence intervals will be calculated and evaluated using a 95% two-sided confidence level.

Safety analysis is aimed at estimating the number and percentage of patients dropped out due to AEs, the number of patients who have experienced at least one AE, the most frequent AEs and the number of patients who experienced at least one SAE. The 95% confidence intervals will be also determined. Safety evaluation will be performed with intention-to-treat analysis.

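### Echo change is counted from the screening echo, and entry requires a low echo LVEF, so within-arm echo gains, and their comparison with angiographic change, probably carry some regression to the mean

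*Protocol article*

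**What the plan says.** All references are to the protocol article.

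- **Echo baseline** (Echocardiographic measurement of ventricular function): "LV function will be measured with echocardiography at baseline (visit 1) as well as 6 (visit 5"; follow-up echoes continue to month 24.
- **Visit 1 is screening** (Trial design): "screening (visit 1), randomization (visit 2), infusion (visit 3".
- **Entry threshold** (Table 1, inclusion criterion 7): LVEF of at most 40%, "or LVEF 40–50% if left ventricular end diastolic volume (LVEDV) > 110 ml/m^2^ (measured by echocardiogram".
- **Angiographic LVEF** (Study outcomes): measured twice, "on the date of the intracoronary infusion of either experimental treatment or placebo (visit 3) and at month 6 (visit 5) after infusion".
- **Analysis** (Data management and statistical analysis): quantitative efficacy parameters are evaluated by "comparing basal values (prior to the administration of the product) with those recorded in the follow-up visits, using the paired Student’s t-test", or by the Wilcoxon paired test. That section names no between-arm test for them.
- **Comparison of methods** (Echocardiographic measurement): "LVEF changes trends measured with LV angiography will be compared with those obtained using echocardiography". The intra-subject correlation is also to be analysed, and the result is meant to help explain short- and long-term effects. The Discussion repeats this aim.

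**The concern.** When a measurement must fall below a ceiling for a patient to enter, and the same measurement then serves as baseline, its random error is selected to be negative on average. Later readings drift back up without any treatment effect. Echo change from visit 1 would carry this drift in both arms. Angiographic change from visit 3 to visit 5 carries little or none, because neither of its readings decided entry.

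Two planned uses are exposed:

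1. The paired within-arm test would tend to credit the drift to treatment.
2. Setting echo trends beside angiographic trends would show an echo excess that comes from the choice of baseline, not from the method or the cells.

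This matters because no angiogram is scheduled after month 6, so the LVEF evidence at months 12 to 24 is echo alone.

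**Working it through.** **1. The plan's own figure.** From Sample size calculation: SD 10, correlation 0.5, difference 9 units, two-sided alpha 0.05, power 0.80, allocation 2:1, 10% loss.

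- SD of change = √(2 × 10² × (1 − 0.5)) = 10.
- Control n = 1.5 × (10 × (1.960 + 0.842) / 9)² = 14.5, so 15; active n = 30.
- 15/0.9 = 16.7 and 30/0.9 = 33.3, so 17 and 34.

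The stated 17 + 34 = 51 is reproduced, and the present point does not affect it.

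**2. Inputs for the bias.** SD 10 and correlation 0.5 are the plan's values. They were set for the primary endpoint, so using them for echo is an assumption. Also assumed: pre-selection mean LVEF μ of 28 to 35, repeat correlation ρ up to 0.9, and a fraction f of 0 or 0.5 of the 40–50% band admitted through the volume route.

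**3. Formula.** With no true change, c₁ = (40 − μ)/10 and c₂ = (50 − μ)/10,

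expected change = (1 − ρ) × 10 × [(1 − f)φ(c₁) + fφ(c₂)] / [(1 − f)Φ(c₁) + fΦ(c₂)].

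Example with μ = 35 and ρ = 0.5:

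- f = 0: 0.5 × 10 × 0.352/0.691 = 2.55.
- f = 0.5: 0.5 × 10 × (0.176 + 0.065)/(0.346 + 0.467) = 1.48.

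**4. False positives.** These are chances of a significant gain from a two-sided 5% paired t-test, n = 34, using the noncentral t with the SD of change after selection. In the f = 0 example that SD is 9.34, so the noncentrality is 2.55/(9.34/√34) = 1.59 and the rate is 34%.

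| μ | ρ | Gain, f = 0 | False positive | Gain, f = 0.5 | False positive |
|---|---|---|---|---|---|
| 28 | 0.5 | 1.1 | 10% | 0.6 | 5% |
| 28 | 0.9 | 0.2 | 5% | 0.1 | 4% |
| 30 | 0.5 | 1.4 | 14% | 0.8 | 7% |
| 30 | 0.9 | 0.3 | 6% | 0.2 | 4% |
| 35 | 0.5 | 2.55 | 34% | 1.5 | 14% |
| 35 | 0.8 | 1.0 | 15% | 0.6 | 8% |
| 35 | 0.9 | 0.5 | 10% | 0.3 | 6% |

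**5. The other measurements.** Simulating all four readings (echo at visits 1 and 5, angiogram at visits 3 and 5), with selection on the visit-1 echo only and no treatment effect, gave an angiographic change of about 0.0. The between-arm difference in echo change was also about 0.0. The offset between the two methods' trends is therefore the whole echo gain in the table. The simulation lets visit-1 error be independent of visit 3. A real dip lasting from visit 1 to visit 3 would pass a little of the bias to angiography, hence 'little or none'.

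**6. Extreme setting.** μ = 40, ρ = 0.5 and a hard cut give 4.0 units and 69%. Enrolled patients would then have a baseline SD of 6.0 and a baseline-to-final correlation of 0.33, well below the plan's 10 and 0.5.

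**The case against.** **The premise is inferred.** No sentence says that the visit-1 echo decides entry. Patients are already followed in the participating cardiology units, were diagnosed by echo at least six months earlier, and could have been identified on an earlier clinical echo. The visit schedule is in a figure that is not shown. This stands, so the point must be conditional. The inference remains the natural one: criterion 7 needs an echo LVEF, visit 1 is screening, and the text mentions no other pre-infusion echo.

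**The size may be small.** Correlation 0.5 is a planning value for initial against final LVEF, not echo repeatability, and variation in true response lowers it. The pilot also hints at low LVEF. If the 20 of 27 patients with a gain are the responders, the final mean is (20 × 38 + 7 × 27)/27 = 35.1, and subtracting 9.4 gives a baseline near 26. A pre-selection mean of 28 with a hard cut yields an enrolled mean of 25.8. This stands, and it is why the range starts near 0.1 units. Even the 2.55-unit setting implies an enrolled SD of 7.0 and correlation of 0.37.

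**Randomisation protects the contrast.** Both arms are selected alike, so a between-arm echo comparison is unbiased. This stands and is the basis of the fix. It does not rescue the analysis as stated, which is paired within patients, nor the raw trend comparison.

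**The comparison of methods is already hedged.** The article says that the two estimates are not interchangeable. That caveat concerns level and technique, not a baseline that is selected in one method only.

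**Conclusion.** The point holds in conditional form. If the visit-1 echo is the qualifying echo, within-arm echo change is biased upward and the raw echo-versus-angiography trend comparison contains a systematic offset. The direction is firm. The size, about 0.1 to 2.5 units with 4% to 34% false positives for benefit at n = 34, rests on a pre-selection mean and a repeatability that the document does not give. For scale, the Background cites published gains of about 5.4 units, and comparison with published trials is one stated purpose of the echo measurements.

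A reader might infer more than the document supports:

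- **That the primary endpoint or the randomised contrasts are biased.** They are not: the angiographic baseline did not decide entry, and selection is the same in both arms.
- **That the intra-subject correlation is inflated.** A constant offset does not raise a correlation.
- **That all long-term efficacy rests on echo.** Study outcomes also lists NYHA class, BNP or NT-proBNP and exercise testing. Only long-term LVEF depends on echo.
- **That a false gain is certain, or as likely as 69%.** The lower end is barely above nominal, and the top end needs the extreme setting above.

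This is a modest problem in a secondary outcome, worth correcting because the correction is cheap.

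**What to change.** Change the wording in two sections.

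1. **Echocardiographic measurement of ventricular function:** state whether the visit-1 echo is the qualifying measurement. If it is, say that raw echo change from visit 1 is not to be read as a treatment effect or set against raw angiographic change. Compare the two methods at month 6 on their BMMNC-minus-placebo differences, each adjusted for its own baseline. The intra-subject correlation can stay as a descriptive result.
2. **Data management and statistical analysis:** draw the echo conclusions for months 6 to 24 from the same baseline-adjusted between-arm differences, with within-arm change as description only.

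If a later pre-infusion echo that did not decide entry is already on record, use it as the echo baseline.

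No new scans or patients are needed. The cost is precision and a less favourable-looking echo result. With the plan's SD 10 and correlation 0.5, the standard error of a within-arm mean change is 10/√34 = 1.7 units. For the adjusted between-arm difference it is 10 × √(1 − 0.25) × √(1/34 + 1/17) = 2.6 units. The article reports recruitment as active and no dataset as yet analysed, so on its own account the change could be made before analysis.
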